## Abstract

**Background:**

Warfarin and similar vitamin K antagonists have been the standard therapy for patients with mechanical or biological valve prosthesis and atrial fibrillation (AF). Even with the appropriate use of therapy, some studies have reported that there is a high incidence of thromboembolic events, 1%-4% per year. Furthermore, a bleeding risk is significant, ranging from 2% to 9% per year, according to some studies.

**Objective:**

The objective of our study was to examine the effect of dabigatran etexilate versus dose-adjusted warfarin for the prevention of intracardiac thrombus in persistent or permanent AF at least 3 months after aortic and/or mitral bioprosthesis replacement.

**Methods:**

Dabigatran versus warfarin after bioprosthesis valve replacement for the management of atrial fibrillation postoperatively (DAWA) is a phase 2, prospective, open label, randomized exploratory pilot study. The main variable to be observed in this study is intracardiac thrombus. From August 2013 to April 2015, 100 patients, at least 3 months after aortic and/or mitral bioprosthesis replacement and permanent or persistent AF postoperatively, who match eligibility criteria will be selected from Ana Nery Hospital in Salvador-Bahia with a follow-up of three months. Patients were randomly assigned in a 1:1 ratio to receive either dabigatran etexilate or warfarin.

**Results:**

Although the present study has no statistic power to proof non-inferiority, it is expected that the dabigatran etexilate group will be protected as well as the warfarin group from intracardiac thrombus, without increasing the bleeding rates, since we are using safer doses (110 mg bid). The lack of necessity of monitoring INR is also another factor that contributes to a better adherence to the new drug and it can make all the difference in the manner of doing anticoagulation for patients with similar clinical characteristics.

**Conclusions:**

The study is in the recruitment phase. It is possible that dabigatran etexilate is as effective as warfarin in preventing the emergence of intracardiac thrombus in patients with AF and mitral and/or aortic bioprosthesis.

**Trial Registration:**

Clinicaltrials.gov NCT01868243; http://clinicaltrials.gov/ct2/show/NCT01868243 (Archived by WebCite at http://www.webcitation/6OABiuasd).

## Introduction

### Overview

Valvular heart disease affects over 100 million people worldwide. Its prevalence is rising due to the high incidence of rheumatic disease in developing countries and the growing impact of degenerative valve disease in elderly populations, a consequence of population ageing [1,2]. An estimated 4 million valve replacement procedures have been performed in the last 50 years, and it remains the only definitive treatment for most patients with advanced heart valve disease [3].

### Warfarin

Warfarin and similar vitamin K antagonists (VKA) have been the standard therapy for patients with a prosthetic heart valve and atrial fibrillation (AF). Even with the appropriate use of therapy, the incidence of thromboembolic events is still substantial, 1%-4% per year. Furthermore, bleeding risk is significant, ranging from 2% to 9% per year [3-5]. VKA have a narrow therapeutic index and also a complex pharmacology, for example, a long pharmacologic inertia and common interaction with other drugs [6]. These features make the management of these drugs a challenge for physicians and their patients.

### Dabigatran Etexilate

Dabigatran etexilate is the prodrug of dabigatran, a direct thrombin (factor IIa) inhibitor. After administration, it is rapidly converted by serum esterase to the active moiety, dabigatran, which is a nonpeptide, potent, competitive, and reversible inhibitor of thrombin. The pharmacokinetics and pharmacodynamics of dabigatran allow fixed dose administration without coagulation monitoring [7].

The US Food and Drug Administration (FDA) approved dabigatran on October 19, 2010, for the prevention of stroke and systemic embolism in patients with nonvalvular AF [8]. The Randomized Evaluation of Long-Term Anticoagulation Therapy (RE-LY) trial [9] was a noninferiority study that compared dabigatran at 2 ﬁxed doses (150 mg twice daily and 110 mg twice daily) with dose-adjusted warfarin (target international normalized ratio, INR range = 2.0-3.0) reaching the criterion of noninferiority for the two doses tested (relative risk, RR = 0.66; 95% conﬁdence interval, CI 0.53-0.82; *P*=.001; and RR=0.91; 95% CI 0.74-1.11; *P*=.34, respectively) [8]. The continued observation of 5851 dabigatran-treated RE-LY patients beyond the randomized trial's follow-up time suggests no significant difference between the two dosages in the trial's primary endpoint, stroke or systemic embolism, however, the 150 mg dosage showed higher rates of major and minor bleeding, without increasing the risk of hemorrhagic stroke [10].

Nevertheless, there are no studies in humans evaluating the efficacy and safety of dabigatran in patients with AF and mitral and/or aortic bioprosthetic valve. Among patients with mechanical heart valves, the randomized phase II study to evaluate the safety and pharmacokinetics of oral dabigatran etexilate in patients after heart valve replacement (RE-ALIGN) was terminated early because the dabigatran etexilate treatment arm had significantly more thromboembolic events (valve thrombosis, stroke, and myocardial infarction) and major bleeding (predominantly postoperative pericardial effusions requiring intervention for hemodynamic compromise) than did the warfarin treatment arm. These bleeding and thromboembolic events were reported in patients who were initiated on dabigatran etexilate postoperatively within 3 days after mechanical bileaflet valve implantation, and in patients whose valves had been implanted more than 3 months previously [11].

With this gap in mind, considering the complicated management of VKAs, the investigators of this study chose to conduct an open randomized controlled pilot trial to assess the efficacy and safety of dabigatran etexilate compared with warfarin in patients with persistent or permanent AF after bioprosthetic mitral and/or aortic replacement (DAWA).

## Methods

### Study Design

DAWA is a phase 2, prospective, open label randomized pilot study. The main variable to be observed in this study is intracardiac thrombus. There are no formal primary or secondary clinical efﬁcacy or safety outcomes because it is a pilot study. Mortality and morbidity events (ischemic and hemorrhagic stroke, systemic embolism, major bleeding, prosthesis valve thrombosis, and any cause of death) will be evaluated in an exploratory manner and are considered as further endpoints in this trial. The inclusion and exclusion criteria are outlined in Textboxes 1 and 2.

The study will be performed in accordance with the ethical principles that have been laid down in the Declaration of Helsinki. They are consistent with the International Conference on Harmonization/Good Clinical Practice, and applicable regulatory requirements in Brazil where it was approved unreservedly by the local ethics and research committee´s under protocol number 14284813.9.0000.0045. A data monitoring committee will monitor patient safety and treatment efficacy every 2 months.

DAWA inclusion criteria.Age from 18 to 64 years at entryPatients with mitral and/or aorthic valve bioprosthesis for at least 3 months postoperativelyThere is 12-lead electrocardiogram documented AF on the day of screening or randomization; or a 24-hour Holter electrocardiogram recording showing AF episodes postoperativelyBrain computed tomography scan without hemorrhage or findings of acute cerebral infarction on the last 2 days of screeningExclusion of atrial thrombus or valve prosthesis thrombosis by transesophageal echocardiograph on the last 2 days of screeningWritten, informed consent

DAWA exclusion criteria.Previous hemorrhagic strokeIschemic stroke in the last 6 monthsSevere renal impairment (creatinine clearance rates < 30 ml/min)Active liver disease (any etiology)Concomitant use of any antiplatelet (aspirin, clopidogrel, prasugrel, ticagrelor, ticlopidine, etc)Increased risk of bleeding (congenital or acquired)Uncontrolled hypertensionGastrointestinal hemorrhage within the past yearAnemia (hemoglobin level <10 g/dL) or thrombocytopenia (platelet count < 100 × 109/L)Active infective endocarditisPregnant or lactating women

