### Randomization and Follow-Up

Prospectively, from August 2013 to April 2015, 100 consecutive patients between 18 and 64 years old, at least 3 months after mitral and/or aortic bioprosthesis valve replacement, documented AF postoperatively, and who match the eligibility criteria are being recruited from Ana Nery Hospital in Salvador-Brazil after obtention of informed consent.

For the allocation of the participants, a computer generated list of random numbers including 1 to 100 was used [12]. Following that, the allocation sequence was concealed (in sequentially numbered, opaque, black, sealed, and stapled envelopes) from the researcher who was enrolling and assessing participants. By convention, every “even number” is being allocated to the dabigatran etexilate group and every “odd number” to the warfarin group, that was consecutively selected blindly from the previous list, thereby selecting exactly 50 patients in each group (1:1 allocation), (Figure 1 shows this grouping). After this randomization, patients had study visits scheduled at 7 days (via telephone) and at 30 days (personally). The enrollment period was 21 months with a planned minimum follow-up period of 3 months.

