### Outcomes

The primary endpoint will be the appearance of an intracardiac thrombus in an esophageal echocardiogram to be held at the end of the follow-up. Other probable endpoints are the composite of stroke (ischemic or hemorrhagic), systemic embolism (to the central nervous system or peripheral), and prosthesis valve thrombosis. The safety endpoints will be any bleeding event (major or minor), elevated liver enzymes, or hepatic function abnormalities.

A thromboembolic event involving the central nervous system was defined as a sudden, focal neurological deficit of presumed vascular origin lasting 24 hours to 7 days (reversible ischemic neurological deficit) or enduring more than 7 days (stroke), as confirmed by computed tomographic or magnetic resonance scan imaging and evaluated by a skilled physician. A peripheral embolism was diagnosed when there was a sudden onset of arterial occlusion in the extremities (with or without cyanosis) and with reported absence of pulse, or sudden abdominal pain requiring urgent intervention (confirming acute intestinal ischemia during the surgical procedure). One of the criteria in the list below defined a major bleeding event [19]. All other bleeding will be considered minor and will also be computed.

Major bleeding criteria: (1) fatal bleeding, (2) symptomatic bleeding in a critical area or organ, such as intracranial, intraspinal, intraocular, retroperitoneal, intraarticular or pericardial, or intramuscular with compartment syndrome, and/or, (3) bleeding causing a fall in hemoglobin level of 20 g L^-1^(1.24 mmol L^-1^) or more, or leading to transfusion of two or more units of whole blood or red cells.

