### Safety Monitoring

Any patients with bleeding on dabigatran etexilate or warfarin therapy will be immediately hospitalized and screened for the severity of bleeding (mild, moderate, or life-threatening bleeding). The management of these complications will follow current guidelines and review articles [13-18].

All participants will have telephone visits scheduled weekly. After that period, study visits will be scheduled monthly. The telephone number of all the researchers will also be available to the patients. At any time, in any phase of the study, the patient will have the full right to request exclusion from the study.

*Electrocardiography* and laboratory tests (blood count, renal function, electrolytes, and liver function tests) will be performed monthly to monitor any changes that indicate bleeding or coagulopathy. Before the randomization and after the follow-up period, patients will undergo a brain computed tomography without contrast to exclude recent ischemic or previous hemorrhagic cerebrals events, and a transesophageal echocardiogram to check prosthesis function (including peak and mean gradient), and to check left atrial thrombus.

During the follow-up, if any unfavorable outcome with patients in the study is evidenced, an emergency meeting with the ethics committee will be held to evaluate the discontinuation of the study, regardless of their stage of recruitment. Other than that, every 2 months there will be a meeting with the same group with the intention of observing the progress of the study and the outcomes observed in each patient.

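### The open-label trial rests its primary endpoint on a reader's call of thrombus on TEE, and no masked reading is described

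*Protocol article*

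**What the plan says.** The protocol article calls the trial open label in the Abstract and again under Study Design: "DAWA is a phase 2, prospective, open label randomized pilot study". The Outcomes section sets the endpoint: "The primary endpoint will be the appearance of an intracardiac thrombus in an esophageal echocardiogram to be held at the end of the follow-up". The Safety Monitoring section repeats the examination before randomization and after follow-up, alongside a brain CT, and describes it as "a transesophageal echocardiogram to check prosthesis function (including peak and mean gradient), and to check left atrial thrombus". Neither section says who reads the recordings or what the reader knows.

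The one concealment measure is in the Randomization and Follow-Up section, where the allocation sequence is "concealed (in sequentially numbered, opaque, black, sealed, and stapled envelopes) from the researcher who was enrolling and assessing participants". The reference there to blind selection concerns drawing from the number list. For neurological events, the Outcomes section requires imaging confirmation and that the event be "evaluated by a skilled physician". It does not mention masking. The data monitoring committee and the two-monthly meetings are oversight, not endpoint adjudication.

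**The concern.** Once the envelope is opened, everyone involved may know the drug. Whether an image shows thrombus is a matter of interpretation. The Outcomes section sets out criteria for neurological events, peripheral embolism and major bleeding, but none for thrombus on TEE, so equivocal images are left to the reader.

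A reader who knows the arm could be influenced in either direction. The Results section expects dabigatran to protect similarly to warfarin. The Introduction and Discussion describe a mechanical-valve trial stopped early for excess thromboembolism and bleeding on dabigatran. The first could make a reader slower to call thrombus on dabigatran, the second quicker.

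At stake is the one comparison the trial is built around. A small pilot can be imprecise and still be useful. A differential reading error is not reduced by enrolling more patients, and it would carry over into the planning of a later trial.

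**Working it through.** **1. Inputs.**
- From the article: open label (Study Design); binary image endpoint (Outcomes); 50 per arm, "thereby selecting exactly 50 patients in each group (1:1 allocation"; chi-square or Fisher exact test for categorical variables (Statistical Considerations).
- Not in the article: an expected TEE thrombus rate, a rate of equivocal images, a significance level. Values used for these below are assumptions.

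**2. The plan's own figure.** Even and odd numbers from 1 to 100 number 50 and 50, so the 50 per arm is reproduced. The article gives no power calculation to reproduce.

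**3. Weight of one call.** 1/50 = 2 percentage points in that arm's rate.

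**4. Effect on the test.** For k thrombi against 0 with 50 per arm, the two-sided Fisher p-value is 2 × C(50,k) / C(100,k), where C(n,k) is the number of ways to choose k from n:

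| Split | p |
|---|---|
| 1 v 0 | 1.00 |
| 2 v 0 | 2 × 1225/4950 = 0.49 |
| 3 v 0 | 0.24 |
| 4 v 0 | 0.12 |
| 5 v 0 | 0.056 |
| 6 v 0 | 0.027 |

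At an assumed two-sided 0.05 level, a single call is decisive only at the boundary, for example between 5 v 0 and 6 v 0. Away from it, one or two calls change the estimate but not the test result.

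**5. Possible size of a bias (all rates assumed).** Let t be the true thrombus rate, equal in both arms, q the share of equivocal images, and f_W and f_D the fractions of these called thrombus on warfarin and dabigatran. The observed rates are t + q·f_W and t + q·f_D, so the spurious difference (dabigatran minus warfarin) is q × (f_D − f_W).
- *Mild:* q = 10% to 20%, fractions differing by 10 to 20 points. 0.10 × 0.10 = 1 point, up to 0.20 × 0.20 = 4 points, or 0.5 to 2 patients per 50.
- *Strong, favouring dabigatran:* q = 4% to 10%, f_W = 0.5, f_D = 0. The difference is −2 to −5 points. With t = 2% to 5% the relative risk runs from 0.02/0.07 = 0.29 to 0.05/0.07 = 0.71.
- *Strong, against dabigatran:* same q and t, f_W = 0.25, f_D = 0.75. The difference is +2 to +5 points. The relative risk runs from 0.08/0.06 = 1.33 to 0.095/0.045 = 2.11.

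In every case the true difference is zero.

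**The case against.** The strongest reply is that the point rests on silence. Open label describes treatment and is compatible with a masked reader. The article condenses a fuller protocol that may describe the reading procedure. This stands as a limit on wording: one can say that no masked reading is described, not that none takes place. It does not dispose of the point. Assessor masking is a core design feature that an article on an open-label trial would normally report, and this article goes as far as describing the envelopes' colour and that they were stapled.

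The second reply is that this is an exploratory pilot, without formal outcomes or a claim of power, so no confirmatory decision hangs on it. That tempers the consequence. Yet the Outcomes section names a primary endpoint, the Statistical Considerations section plans an intent-to-treat primary analysis, and the Discussion speaks of testing a hypothesis of similar efficacy.

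A reader might also infer more than the documents support:
- *That the same team enrols, adjusts INR and reads the endpoint.* The article does not say who adjusts INR or who reads the TEE. The phrase "from the researcher who was enrolling and assessing participants" may refer to assessing eligibility.
- *That the skilled physician is the TEE reader.* That phrase belongs to the definition of neurological events.
- *That the 1%–4% per year in the Introduction gives the expected number of thrombi.* A quarter of it is 0.25%–1% in three months, but it is a clinical thromboembolic rate, not the rate of thrombus on a scheduled TEE.
- *That one or two equivocal readings settle the result.* 2 v 0 gives p = 0.49.
- *That the bias could never be corrected.* Stored recordings could be re-read masked later. The article does not say whether they are stored.

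**Conclusion.** The point holds in this form: the trial is open label, its primary endpoint is a judgement on an image, and no masked reading is described. Concealing the sequence does not protect the reading. The firm figure is 2 percentage points per changed call, from 50 per arm. The direction of any bias is unknown and its size cannot be estimated from the document. The 1 to 5 points shown above, in either direction, rest wholly on assumed rates of equivocal images and assumed reading habits, and they serve only to show that a false difference of this order is plausible. The article does not establish that any reader knew the arm, nor that a test result would be overturned. The change is worth making because it is cheap and the endpoint is central.

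**What to change.** In the Outcomes and Safety Monitoring sections, state that:
- the end-of-follow-up TEE and brain CT recordings are stored under a code;
- the existing readers interpret them without knowledge of arm or INR, both of which are withheld from the request form;
- the thrombus call is recorded before the arm is revealed;
- the call made from the coded recording is the primary endpoint.

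The last item matters because the operator of a live TEE may learn the drug from the patient, so masking at the bedside may be imperfect.

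The article reports that recruitment is still under way, so the change can apply to examinations yet to come. It can also apply to earlier ones if their recordings were kept. If masked reading is already the practice, one sentence saying so settles the point.

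The cost is a small logistic burden for coding recordings and request forms. No additional reader or procedure, masking of the drugs or change of sample size is needed.

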### Randomization and Follow-Up

Prospectively, from August 2013 to April 2015, 100 consecutive patients between 18 and 64 years old, at least 3 months after mitral and/or aortic bioprosthesis valve replacement, documented AF postoperatively, and who match the eligibility criteria are being recruited from Ana Nery Hospital in Salvador-Brazil after obtention of informed consent.

For the allocation of the participants, a computer generated list of random numbers including 1 to 100 was used [12]. Following that, the allocation sequence was concealed (in sequentially numbered, opaque, black, sealed, and stapled envelopes) from the researcher who was enrolling and assessing participants. By convention, every “even number” is being allocated to the dabigatran etexilate group and every “odd number” to the warfarin group, that was consecutively selected blindly from the previous list, thereby selecting exactly 50 patients in each group (1:1 allocation), (Figure 1 shows this grouping). After this randomization, patients had study visits scheduled at 7 days (via telephone) and at 30 days (personally). The enrollment period was 21 months with a planned minimum follow-up period of 3 months.

**Figure 1 figure1:**
[figure not shown]
DAWA study.

### Drug Administration Protocol

Dabigatran etexilate will be supplied as capsules containing 110 mg, which should be taken twice daily without the need of INR monitoring. All the patients randomized to use dabigatran etexilate will remain with that drug for the duration of the study. Any patients who used warfarin previously will do a drug washout, followed by an immediate introduction of dabigatran etexilate once the INR < 2.5.

The patients assigned to warfarin will require close coagulation monitoring to achieve the target INR (range, 2.0-3.0). Therefore, it will be necessary to follow a protocol of monitoring and dosage adjustment of this drug to ensure the safety and optimization of its use since each patient responds differently to the same doses. The warfarin dose adjustment algorithm was made according to the evidence-based guideline of the American College of Chest Physicians, and several other studies [6,13-18]. Doses between 5 mg and 10 mg were administered for the first days for most individuals, with subsequent dosing based on INR response. The patients should have a baseline prothrombin time/INR checked prior to initiating warfarin therapy, and rechecked 2-3 days after initiating therapy, and then checked again every 2-3 days until stable. After this, they will be rechecked after 15 days, and if they are stable, every 30 days.

### Outcomes

The primary endpoint will be the appearance of an intracardiac thrombus in an esophageal echocardiogram to be held at the end of the follow-up. Other probable endpoints are the composite of stroke (ischemic or hemorrhagic), systemic embolism (to the central nervous system or peripheral), and prosthesis valve thrombosis. The safety endpoints will be any bleeding event (major or minor), elevated liver enzymes, or hepatic function abnormalities.

A thromboembolic event involving the central nervous system was defined as a sudden, focal neurological deficit of presumed vascular origin lasting 24 hours to 7 days (reversible ischemic neurological deficit) or enduring more than 7 days (stroke), as confirmed by computed tomographic or magnetic resonance scan imaging and evaluated by a skilled physician. A peripheral embolism was diagnosed when there was a sudden onset of arterial occlusion in the extremities (with or without cyanosis) and with reported absence of pulse, or sudden abdominal pain requiring urgent intervention (confirming acute intestinal ischemia during the surgical procedure). One of the criteria in the list below defined a major bleeding event [19]. All other bleeding will be considered minor and will also be computed.

Major bleeding criteria: (1) fatal bleeding, (2) symptomatic bleeding in a critical area or organ, such as intracranial, intraspinal, intraocular, retroperitoneal, intraarticular or pericardial, or intramuscular with compartment syndrome, and/or, (3) bleeding causing a fall in hemoglobin level of 20 g L^-1^(1.24 mmol L^-1^) or more, or leading to transfusion of two or more units of whole blood or red cells.

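### The peripheral embolism definition is narrower than the systemic embolism endpoint it serves: emboli outside the limbs and bowel, and bowel emboli not confirmed at surgery, are not counted

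*Protocol article*

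**What the plan says.** In the protocol article, Methods, Outcomes, one component of the non-primary composite is "systemic embolism (to the central nervous system or peripheral), and prosthesis valve thrombosis". Systemic embolism thus has two classes, central nervous system and peripheral, and no third.

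The same section then defines the peripheral class by two routes:

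- Limb: "sudden onset of arterial occlusion in the extremities (with or without cyanosis) and with reported absence of pulse".
- Abdomen: "sudden abdominal pain requiring urgent intervention (confirming acute intestinal ischemia during the surgical procedure".

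For central nervous system events, the standard of proof is different: "as confirmed by computed tomographic or magnetic resonance scan imaging and evaluated by a skilled physician".

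Methods, Study Design, lists "systemic embolism, major bleeding, prosthesis valve thrombosis, and any cause of death" among the morbidity and mortality events and says that these "will be evaluated in an exploratory manner and are considered as further endpoints in this trial". It names systemic embolism but does not define it.

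**The concern.** An endpoint named for systemic embolism should count an arterial embolus wherever it lodges. The definition instead lists two clinical pictures and stops. It has no residual category and no wording that marks the two routes as examples. The major bleeding criteria in the same section do introduce their critical sites as examples.

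Two things are at stake. First, a true embolus can occur and be well documented, yet not be an event. Second, the abdominal route makes the outcome depend partly on treatment: the same bowel embolus counts if the patient is operated on and does not count otherwise. The trial is open label, so the decision to operate can be taken with knowledge of the assigned drug.

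**Working it through.** The article states no event count or power figure for this endpoint, so there is no figure to reproduce. The check is a reading of the definition against typical cases, followed by a calculation for scale.

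**Step 1: cases against the two routes**

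| Case | Limb route | Abdominal route | Counted as systemic embolism? |
|---|---|---|---|
| Limb occlusion, pulse absent (with or without imaging) | met | n/a | yes |
| Limb occlusion on imaging, pulse preserved | fails | n/a | no |
| Bowel ischaemia confirmed at surgery after sudden pain | n/a | met | yes |
| Mesenteric occlusion on imaging, no surgery | n/a | fails | no |
| Renal or splenic embolus | n/a | fails | no |
| Embolus first found at autopsy | fails | fails | no (the death counts as death from any cause) |

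Imaging does not exclude a case. What fails is an embolus shown by imaging alone. Every mention of embolism in the article was checked, and none widens the definition.

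**Step 2: size of the pool**

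Inputs:
- 100 patients, 50 per arm (Randomization and Follow-Up).
- 3 months of follow-up, 0.25 year (Abstract; given as a minimum in Randomization and Follow-Up).
- 1%-4% per year for all thromboembolic events on vitamin K antagonists (Introduction, Warfarin).
- Assumptions: the same rate in both arms, constant over time.

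Risk per patient, p = annual rate x 0.25:
- 0.01 x 0.25 = 0.0025
- 0.04 x 0.25 = 0.01

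Expected events in the whole trial, 100 x p: 0.25 to 1.0 (per arm, 50 x p: 0.125 to 0.5).

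P(at least one event) = 1 - (1 - p)^100:
- 1 - 0.9975^100 = 0.22
- 1 - 0.99^100 = 0.63

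**Step 3: what might be lost**

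The share m of thromboembolic events that the definition misses is not in the documents. The values below are assumptions that show the range. Counted events = 100 x p x (1 - m); lost events = 100 x p x m.

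| m (assumed) | Expected counted | Expected lost | P(at least one counted) |
|---|---|---|---|
| 10% | 0.23-0.90 | 0.025-0.10 | 0.20-0.60 |
| 30% | 0.18-0.70 | 0.075-0.30 | 0.16-0.50 |
| 50% | 0.13-0.50 | 0.125-0.50 | 0.12-0.39 |

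**Step 4: effect on the comparison**

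Let the true risks be pD and pW and the fractions captured sD and sW, with no false events. The observed ratio is (sD x pD)/(sW x pW).
- If sD = sW = s, the ratio is pD/pW, unchanged, and the difference shrinks to s x (pD - pW).
- If sD differs from sW, the ratio is biased by the factor sD/sW.

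The decision to operate is one way in which sD and sW could come to differ. The documents give no figure for it.

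**The case against.** The strongest case against is that little rests on this definition. The endpoint is exploratory, the article disclaims power to prove non-inferiority, and no test or decision rule uses peripheral embolism. The definition is explicit and worded identically for both arms. The expected loss is a fraction of an event, so the likeliest effect on the data is none. Safety oversight (the data monitoring committee and the emergency ethics meeting) is not tied to this definition, so such events would not be invisible. All of that stands and limits the weight of the point. It does not make the definition fit the endpoint's name.

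A reader might infer three stronger things that the documents do not support:

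- *That under-counting favours the result the article expects.* The expectation of equal protection in the Abstract and Results concerns intracardiac thrombus. That is the primary endpoint, assessed by echocardiography, and this definition does not touch it. Equal proportional under-counting also leaves the ratio unbiased.
- *That 0.125-0.5 events per arm, or 2 percentage points (1/50), measures the loss.* The first is the whole thromboembolic pool, not the share missed. The second presupposes that an event has been lost and would apply to any misclassified event.
- *That the limb route is too loose and should require objective confirmation.* It already requires arterial occlusion together with an absent pulse. Adding a confirmation requirement would remove events from a sparse endpoint; that is a debatable trade-off, not an error.

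**Conclusion.** The point holds as a mismatch between an endpoint and its definition. As written, renal and splenic emboli, mesenteric occlusion shown on imaging without surgery, and emboli first found at autopsy are not systemic embolism events. Whether a bowel embolus counts depends on a decision to operate in an open-label trial. This is a rule that the article itself fixes, not a detail left to a fuller document.

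The consequence is small in expected number: under-counting within a pool of about 0.25-1.0 thromboembolic events in the whole trial. This assumes 1%-4% per year in both arms, a constant rate and 3 months of follow-up for all 100 patients. The share missed is unknown. The primary endpoint is not affected. The absolute difference shrinks under equal under-counting, and the risk ratio is biased only if under-counting differs by arm, which is possible here but not shown. The change is worth making because it is cheap and, with so few events expected, one uncounted embolus could be the only one in an arm.

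**What to change.** Replace the definition in Methods, Outcomes, with one that covers acute arterial occlusion or infarction at any site outside the central nervous system, documented by imaging, surgery or autopsy. Remove the condition that bowel ischaemia be confirmed during an operation. Keep the existing clinical limb criterion as a qualifying route, so that no event counted now is lost.

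The cost is one sentence. The evidence comes from usual-care imaging, operative and autopsy findings, so no visit, test or change in sample size is needed. The article describes the study as still recruiting, so the wording can be changed before the final analysis and applied to all patients. The small downside is that events already classified must be re-reviewed under the new wording.
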